## Materials and Methods

### Study Design

The study is a prospective randomized placebo controlled, parallel-group trial that will be conducted at the Affiliated Hospital and the Second Clinical Medical College of North Sichuan Medical University. The protocol has been registered with the China Clinical Trial Registry (item number: ChiCTR2100050753). Our study will show improvement in cognitive function in patients with TBI following rTMS bilateral DLPFC intervention. The findings may provide a rationale for an approach of rTMS intervention for cognitive function in patients with TBI. Thirty-six patients with TBI will be enrolled in the trial. The physicians will provide patients with detailed information about the trial in verbal and written form before the trial begins.All patients will voluntarily sign an informed consent form. All patients will be screened according to eligibility criteria. 36 subjects will be randomized in a 1:1:1 ratio into the real-rTMS group, the Cognitive training group and the sham-rTMS group. All subjects will be required to perform neuropsychological assessments at before intervention, post-10 sessions, post-20 sessions, and 30 days after the intervention. MRI will be performed at pre-intervention and post-20 sessions. All patients will receive intervention for 4 weeks (30 minutes per day, 5 days per week). The diagram and schedule for the study are shown in Figure 1 and Table 1.

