### rTMS

rTMS with a focal figure-of-8-shaped coil (i.e., active and sham coils) will be performed among all participants. The sham coil has the same size and shape as the active coil. However, it does not create any significant magnetic field.

The coils of the transcranial magnetic stimulator will be placed on the patient's left and right dorsolateral prefrontal cortices (DLPFC) based on the F3 and F4 positioning specified in the International 10–20 system for conducting electroencephalography (EEG) (24). The stimulation intensity will be set at a 100% threshold by measuring the threshold of the hallux abductor muscle. rTMS will be delivered to the left DLPFC at a frequency of 10 Hz (5 s durations, 25 s pauses) for a total of 2,000 pulses (50 pulses per train, 40 trains). rTMS will likewise be delivered to the right DLPFC at a frequency of 1 Hz (5 s durations, 25 s pauses) for a total of 2,000 pulses (40 pulses per train, 50 trains). There will be a total of 20 intervention sessions.

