#### Cognitive Training

Subjects will be given computer-assisted cognitive training. The computer system is used for cognitive function training, and patients are guided by professionally trained therapists. The task areas include: (a) visuospatial training; (b) executive function and problem solving; (c) attention training; (d) memory training; and (e) calculation training. There are over 20 different therapeutic tasks for training, and the difficulty of the tasks in each area increases automatically as the participant successfully performs the simpler tasks. The cognitive training schedule was 30 min/session, 1 session/day, 5 days/week, with a treatment period of 4 weeks.

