### Dropout Criteria

The intervention will be discontinued if the subject meets one or more of the following criteria (a) Subjects who are enrolled incorrectly; (b) Subjects have poor compliance and do not follow treatment as required, as when subjects fail to cooperate with investigators, or when subjects are unable to remain quiet and immobile, or when subjects do not come to treatment on time; (c) Inadequate medical record that interferes with efficacy or safety evaluation; (d) Subjects drop out voluntarily; (e) The subject develops adverse events (including seizures, pain, irritability, etc.); (f) There is severe progression of the subject's condition or some comorbidities, complications, or specific physiological changes; and (g) The subject is considered by the investigator to be unsuitable for further participation in this study.

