### Outcome Measures

The primary outcome of the proposed study is current executive functioning as measured by the Shape Trail Test (STT), which was revised for the Chinese-speaking population based on the Trail Making Test (TMT). The secondary outcome measures are neuropsychological test findings based on the Hopkins Verbal Learning Test (HVLT), the Brief Visuospatial Memory Test (BVMT), and the Digit Span Test (DST), as well as evaluations of the safety and tolerability of rTMS in patients with TBI.

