### Data Collection and Management

The trial process will be recorded via audio or in a written form to assure the authenticity of the intervention. A case report form (CRF) will be used to collect data. Two data managers will enter the data from the CRF into computer databases and will cross-check the uniformity of the hardcopy and electronic data. During the enrollment phase, each participant will remain anonymous through an assigned identifier. Only the CRF will record the patient's identifying information. All data are confidential to anyone external to the study with the exception of the ethics committee. Experimental data will be used to write clinical research articles. Experimental data will be used to write clinical research articles. Regarding the MRI data, we will obtain consent from the participants to keep the data in the hospital for future studies. During the process of the study, if participants discontinue or deviate from the intervention protocol, we will collect as much data as possible for further analysis.

We will use the following methods to facilitate participants' completion of the trial and follow-up: (a) enhancing communication between investigators and patients to gain patients' cooperation to the extent possible; (b) providing financial compensation according to the number of patients' study visits in order to encourage patients to continue to participate in the trial; and (c) providing free relevant examination results to study patients, including the results of cognitive assessments.

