### Statistical Analysis

Baseline comparisons were used to examine potential differences between real-rTMS, sham-rTMS, and cognitive training, which ensured that there are no differences between the three groups. Potential baseline differences between the three groups will be detected. Gender, education, and pathological characteristics (axonal injury or cerebral hemorrhage) will be measured using Chi-square tests. The One-way ANOVA is conducted to analyze the outcome and information of the pre-intervention assessment. The Kolmogorov-Smirnov test will be used to evaluate the normality of distributions. If a normal distribution is confirmed, data will be presented as means and standard deviations (SD) and ANOVA will be used to analyze the effects at T1, T2, T3, and T4, with Bonferroni correction for multiple comparisons as a *post hoc* test. if it does not conform to a normal distribution, it will be tested using Kruskal-Wallis (non-parametric test). *P*-values <0.05 will be considered statistically significant. Data will be analyzed using the Statistical Package for Social Sciences (SPSS) software (v.22.0; SPSS, Inc., Chicago, IL, USA). MRI data will be examined in statistical parametric mapping using independent Student's *t*-tests. The statistical significance is P <0.001. To find other correlated factors that may have an impact on the efficacy of the intervention, correlations between changes in MRI data and changes in behavioral data will be calculated. Only patients completing the rTMS protocol will be included in analyses.

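### Completers of the rTMS protocol are the only analysis population, so the efficacy comparison depends on post-randomization events and the rule does not fit other parts of the article

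*Protocol article*

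**What the plan says.** All references are to the protocol article.

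- **Analysis set (Statistical Analysis):** "Only patients completing the rTMS protocol will be included in analyses". The sentence is unqualified. It is not described as a per-protocol or sensitivity analysis, and the article names no intention-to-treat or other set.
- **Design (Study Design):** "36 subjects will be randomized in a 1:1:1 ratio into the real-rTMS group, the Cognitive training group and the sham-rTMS group".
- **Reasons to discontinue (Dropout Criteria):** criterion (e) is "The subject develops adverse events (including seizures, pain, irritability, etc".). Other criteria are poor compliance, voluntary withdrawal, severe progression, and the investigator's view that the subject is unsuitable. Potential Pitfalls and Contingency Plans adds that any discomfort stops the intervention.
- **Data after discontinuation (Data Collection and Management):** "if participants discontinue or deviate from the intervention protocol, we will collect as much data as possible for further analysis".
- **Safety:** Outcome Measures lists "evaluations of the safety and tolerability of rTMS in patients with TBI" with the secondary outcomes, and Adverse Events promises descriptive statistics for every adverse event.
- **Third arm (Cognitive Training):** "Subjects will be given computer-assisted cognitive training". That section describes no stimulation, yet the rTMS section says that stimulation, with an active or sham coil, "will be performed among all participants".

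**The concern.** Randomization makes the arms comparable at day 0. A rule that then keeps only patients who finish treatment compares subsets chosen by what happened afterwards. Several reasons for not finishing could be linked both to the arm and to how the patient would have scored on the Shape Trail Test. Some are discretionary, and the staff who deliver the intervention are not among those listed as blinded in the Blinding section. With 12 patients per arm, one or two exclusions are enough to move a result.

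The sentence also governs every analysis in its section, so its conflicts with other sections matter. Data collected after discontinuation would have no stated use. Patients stopped because of an adverse event are candidates for exclusion while safety is an outcome. One of the three arms has no rTMS protocol that it could complete.

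**Working it through.** **1. The plan's own figures.** Sample Size Estimation gives 10 per group plus 2 for dropout, so 10 + 2 = 12 per group and 3 × 12 = 36 in total. The allowance is 2/12 = 16.7% per arm, or up to 6 of 36 patients. The 10 per group is reproduced by a three-group one-way ANOVA F test if the stated 0.7 is read as Cohen's f, with α = 0.05: noncentrality = N·f² = 30 × 0.49 = 14.7, and power is 0.911. The article does not say that this was the method. Its non-inferiority label is a separate matter that does not affect this point.

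**2. Possible bias from excluding non-completers.** The documents give no data on who would drop out, so this is an illustration. Assumptions: no true effect, normally distributed outcome with SD 1, 12 randomized per arm, two arms compared by a two-sided t-test at 0.05, and higher scores better.

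*Worst one-sided case.* The real arm loses exactly its two worst outcomes and the comparator loses none. The expected lowest two of 12 standard normal values are −1.629 and −1.116. The 12 values have expected sum 0, so the remaining 10 have mean

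(1.629 + 1.116) / 10 = 2.745 / 10 = 0.27 SD.

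If only the single worst is lost, the shift is 1.629 / 11 = 0.15 SD.

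*Range by simulation (100,000 null trials per row).* Patients are removed by a prognostic score with the stated correlation to outcome.

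| Lost, real vs comparator | Correlation with outcome | Bias (SD) | False positives favouring real rTMS |
|---|---|---|---|
| any | 0 | 0 | about 2.5% |
| 2 vs 2 | 0.5 | 0 | about 2.8% |
| 2 vs 2 | 1.0 | 0 | about 4.4% |
| 2 vs 1 | 0.5 | 0.06 | about 3.7% |
| 2 vs 1 | 1.0 | 0.13 | about 7% |
| 1 vs 0 | 1.0 | 0.15 | about 6% |
| 2 vs 0 | 0.5 | 0.14 | about 5% |
| 2 vs 0 | 1.0 | 0.27 | about 11% |

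The nominal rate in the favourable direction is 2.5%. In the balanced case with correlation 1.0 the bias is zero, but the error rate still rises, because cutting off the worst values in both arms shrinks the observed spread. If the comparator arm lost its worst patients instead, the bias would have the same size and run against real rTMS.

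**3. Passages side by side.**

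- *Completers only against data after discontinuation.* One section collects data from those who stop or deviate, for analysis. The other leaves them out. The two fit only if the collected data serve an analysis that the article does not name.
- *Completers only against safety.* An adverse event is a ground for discontinuation, so the patient becomes a non-completer. Adverse Events nevertheless promises statistics on all events. Both cannot hold if the completer rule covers every analysis.
- *Completers of rTMS against three arms.* Taken literally, at most 24 of 36 patients (real and sham) could be analysed. The same section compares three groups, and the Introduction and Sample Size Estimation both need the training comparison.

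**4. Effect of the correction on sample size.** None: it stays at 12 per group. If all 12 per group have outcome data, ANOVA power at f = 0.7 is 0.957, against 0.911 with 10.

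**The case against.** Nothing in the article cures the selection on completion, but four limits on the point are fair, and they stand.

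- **Training arm.** A reader might infer that the plan leaves the cognitive training arm out of the analysis. The article does not support that. Statistical Analysis itself compares all three groups, and other sections use rTMS loosely for every arm; Interventions, for example, times everyone's assessments by rTMS session. The likely meaning is completion of the assigned intervention. What remains is wording to correct.
- **Safety.** A reader might infer that patients with adverse events vanish from the safety results and that tolerability will look better than it is. Adverse Events makes a specific promise to describe all events, which is more naturally read as governing safety. The passages conflict, but the article does not show that safety data will be dropped.
- **Direction and size.** It is tempting to say that the bias favours real rTMS, since the sham coil is said to produce no significant field. That would also require patients who stop to be those with worse scores, and the article offers no evidence of this. The criteria apply to all arms, and some, such as incorrect enrolment or inadequate records, are not clearly related to outcome. Sample Size Estimation allows two dropouts in each arm, not two in one.
- **Non-inferiority.** Sample Size Estimation frames the trial as showing that rTMS is not inferior to cognitive training. There, dilution in an all-randomized set can favour the conclusion, so a completer analysis has a proper place. That justifies completers as one of two sets, not as the only one, and the Introduction states a superiority hypothesis.

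A separate analysis plan might define other sets. The article nevertheless states this rule outright, so it is a stated choice and not an omission.

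**Conclusion.** The point holds for the efficacy population. As written, every between-group comparison is conditional on completing treatment, and completion depends on events after randomization that can differ by arm and relate to outcome. The bias cannot be determined from the documents. Under the null with 12 per arm and losses within the plan's allowance, it runs from 0 (losses unrelated to outcome, or balanced) to about 0.27 SD, with favourable false positives of about 11% instead of 2.5%. The upper end assumes that the real arm alone loses exactly its two worst patients, so it is a bound and not a forecast. On data after discontinuation, safety and the training arm, the article is inconsistent and must be reconciled; stronger conclusions are not supported. The sentence should be changed before analysis, because it decides who contributes to every result.

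**What to change.** Replace the last sentence of Statistical Analysis with:

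> The primary analysis includes all randomized participants in their assigned group, using all available T1–T4 assessments whether or not the assigned intervention was completed. An analysis of participants who completed their assigned intervention is also reported, and for any non-inferiority conclusion both must agree. Safety is summarized in everyone who received at least one session of any intervention.

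Then align Data Collection and Management, Outcome Measures, Adverse Events and the rTMS section's statement about all participants with this text. Speaking of the assigned intervention removes the problem with the training arm.

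**Cost.** No extra patients and no change to the discontinuation criteria, which this point does not address. Outcome assessments need to be sought after discontinuation; the article already intends to collect as much as possible, but does not promise the scheduled visits. The estimated effect may be somewhat diluted, which is why both sets are needed for non-inferiority. Participants with no later assessment remain missing under any rule. A mixed model is optional and not part of this correction; the planned ANOVA or Kruskal-Wallis tests can be applied to the corrected population.

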## Discussion

Thus, far, few studies have reported on the effects of rTMS on cognitive improvement in individuals with TBI. We design a random and comparison clinical trial to observe the effectiveness of rTMS and sham rTMS and cognitive training for cognition of TBI patients.

One of the factors to consider when implementing rTMS is the specificity of its stimulation location. the neurobehavioral effects of rTMS can vary dramatically depending on the specific brain region being stimulated. A critical anatomical region for cognitive enhancement through rTMS is the DLPFC. The DLPFC is a brain region involved in cognitive decision-making that regulates task preparation and maintenance as well as task-related attentional focus (33). Numerous studies have indicated that high-frequency rTMS delivered to the left DLPFC may affect attentional control (18, 34). Some studies have also reported on the role of rTMS delivered to the right frontoparietal lobe in the orientation and maintenance of visuospatial attention (20, 35, 36). When low-frequency rTMS was applied to the frontal cortices of healthy volunteers, glucose metabolism was increased at the site of stimulation and in regions of distance connectivity. A recent report by Neville et al. (18) showed no differences in performance on part B of the Connectedness Test (TMT) after 10 sessions of real and sham rTMS in patients with chronic diffuse axonal injury (DAI), indicating that cognitive function was not improved in patients with DAI. However, Tammy et al. (19) reported that 1 Hz of rTMS delivered to the right DLPFC improved cognitive function in TBI patients after 10 sessions. The difference between the previous study is that rTMS will be delivered to different sites including left or right DLPFC.

In our study, we will apply rTMS on bilateral DLPFC, which differs from the previous intervention protocols. It has likewise been reported that rTMS applied to both the left and right DLPFC can be administered in the effective treatment of depression and can improve serum neuron-specific enolase (NSE) and brain-derived neurotrophic factor (BDNF) levels as well as temporal perception in neurologic patients, causing an overall protective effect on neurological function (34, 37, 38). It has been pointed out that HF-rTMS can significantly improve executive function in patients with cerebrovascular disease, and LF-rTMS can improve attention deficit or inattention in patients with depression and schizophrenia (39). In addition to executive function and memory loss, depressed or dryness are also common symptoms in TBI patients, and these long-term mood disorders can also indirectly contribute to cognitive behavior (1). We performed bilateral rTMS on subjects simultaneously, which may improve both the cognitive difficulties driven by neurological injury and the individual's mental status, thus effectively improving the cognitive abilities of TBI patients.

In the proposed study, resting-state functional magnetic resonance imaging (rs-fMRI) will be used to explore the pathophysiological processes mediating TBI cognitive dysfunction through DLPFC stimulation delivered through rTMS. Disruption of brain network connectivity is an important mechanism leading to cognitive dysfunction in TBI (40); cognitive dysfunction may be primarily associated with disruptions to the default mode network (DMN) (41, 42). The DMN is a task-negative network that is preferentially activated when the individual is not concerned with the external environment and involves several internal cognitions, such as autobiographical memory extraction, looking into the future, envisioning others' perspectives, and processing emotional cognition (43). A recent study found that the DMN is not a single network but rather consists of several intertwined networks. The DMN exhibits positive correlations across internal regions as well as negative correlations with relevant regions of external attentional processing (30). A review of 17 original studies conducted in patients with TBI showed that 53% of these studies reported that rTMS promotes increased brain connectivity, 18% reported that rTMS is associated with decreased functional connectivity, and 29% reported no changes in brain connectivity following rTMS (31). The DLPFC is an important component of the DMN network and its use as a rTMS stimulation site may modulate functional connectivity in the DMN. It is possible that connections within and outside the DMN are transmitted through the paracentral hippocampal cortex and posterior cingulate gyrus as nodes for information transmission (44, 45). As shown by Shang et al. rTMS on the left DLPFC alters the resting-state functional connectivity from the DLPFC to the hippocampal parietal, posterior cingulate cortex (PCC)/precuneus regions in the DMN network (16).

As age, education level, TBI severity, and patients' state of consciousness have been reported as factors influencing patients' cognition (8), this study was proposed to conduct subgroup analyses following measurements of baseline levels of RLAS and MoCA to reduce the effects of raw scores on the obtained results. The rTMS in this study applied to two sites of targeting and may have different efficacy in different subjects, providing a new direction for rTMS intervention in cognition in TBI.

## Ethics Statement

The studies involving human participants were reviewed and approved by the Ethics Committee of Nanchong Central Hospital. The patients/participants provided their written informed consent to participate in this study. Written informed consent was obtained from the individual(s) for the publication of any potentially identifiable images or data included in this article.

## Abbreviations

RLAS: Rancho Los Amigos Scale
DST: Digit Span Test
MoCA: The Montreal Cognitive Assessment
rTMS: repetitive transcranial magnetic stimulation
STT: The Shape Trail Test
HVLT: Hopkins Verbal Learning Test
BVMT: Brief Visuospatial Memory Test
fMRI: functional Magnetic Resonance Imaging.
